## 9.8 Assessment of Expectedness by the CI

The CI will also assess all related SAEs for expectedness with reference to the following criteria (**Table 6**).

| Category   | Definition                                                                                                                                                                                                                                                                        |
|------------|-----------------------------------------------------------------------------------------------------------------------------------------------------------------------------------------------------------------------------------------------------------------------------------|
| Expected   | An adverse event that is consistent with known information about the trial related procedures or that is clearly defined in the relevant safety information: DESTINY Investigator Brochure del Nido (v1.0, 30/03/2021) and SmPC Martindale Cardioplegia Concentrate (18/02/2015). |
| Unexpected | An adverse event that is not consistent with known information about the trial related procedures.                                                                                                                                                                         |

**Table 6.** Assessment of expectedness.

The CI will not overrule the severity or causality assessment given by the site PI but may add additional comment on these. If the event is unexpected (i.e. is not defined in the protocol as

an expected event or is not defined in the approved version of the RSI, it will be classified a Suspected Unexpected Serious Adverse Reaction (SUSAR).

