| Serious Adverse Event                         | SAE   | Any untoward medical occurrence or effect that: 
 
• Results in death or is life-threatening
 
• Requires hospitalisation or prolongation of existing hospitalisation
 
• Results in persistent or significant disability or incapacity
 
• Is a congenital anomaly/birth defect
 
• Or is otherwise considered medically significant by the Investigator
 
 |
| Serious Adverse Reaction                      | SAR   | An Adverse Reaction which also meets the definition of a Serious Adverse Event                                                                                                                                                                                                                                                                                                                                                                               |
| Unexpected Adverse Reaction                   | UAR   | An AR, the nature or severity of which is not consistent with the applicable product information (e.g. Investigator Brochure for an unapproved IMP or (compendium of) Summary of Product Characteristics (SPC) for a licensed product). When the outcome of an AR is not consistent with the applicable product information the AR should be considered unexpected.                                                                                          |
| Suspected Unexpected Serious Adverse Reaction | SUSAR | A SAR that is unexpected i.e. the nature, or severity of the event is not consistent with the applicable product information. A SUSAR should meet the definition of an AR, UAR and SAR.                                                                                                                                                                                                                                                                      |

**Table 4.** Definitions of types of adverse events.

 The term life-threatening is defined as diseases or conditions where the likelihood of death is high unless the course of the disease is interrupted.

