## 9.2 Adverse Events - General Recording Requirements

The collection and reporting of Adverse Events (AEs) will be in accordance with the UK Policy Framework for Health & Social Care (2017), the requirements of the Health Research Authority (HRA), and the sponsor's Code of Practice for Research. Definitions of the different types of AEs are listed in table of definitions, section 9.1.

It is routine practice to record adverse events in the patient's medical notes and it is also recommended that this includes the documentation of the assessment of severity and seriousness, and for causality (relatedness) in relation to the intervention(s) in accordance with the protocol. The assessment of causality should be made with regards to the Reference Safety Information (RSI). For the purposes of the DESTINY trial, this will be the Investigator Brochure for del Nido cardioplegia and the Summary of Product Characteristics for St Thomas' cardioplegia.

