## 9.6 Events that require expedited reporting to the Sponsor on the SAE Form

Based on those morbidities identified as important in the recent multi-centre UK study [3], the following SAEs are protocol-defined as expected but must be reported in an expedited manner using the Serious Adverse Event reporting form to enable efficient monitoring of frequency of events; this requirement has been agreed with the DMC prior to commencing recruitment:

- **Death**
- **Extracorporeal life support (ECLS):** Use of extracorporeal support following the index operation, whether started in the operating theatre or in the ICU, and whether the indication was cardiac arrest, low cardiac output state, poor cardiac function, arrhythmia, residual or recurrent cardiac lesion, or sepsis.
- **Major adverse cardiac event:** Includes cardiac arrest, where the child receives any chest compressions or defibrillation; chest reopening on the ICU or ward, for any reason; major haemorrhage in the ICU following surgery, defined as >10ml/kg/hr for 2 consecutive hours; and acute shunt failure, in those with a surgically constructed systemic to pulmonary shunt.
- **Unplanned reoperation/intervention in the early postoperative period:** Cardiac surgical operations with or without cardiopulmonary bypass, or interventional catheter procedures that occur within 30 days after the index operation or within the same hospital admission, not intended during the planning phase. Includes diaphragm plication and pacemaker insertion for surgically acquired arrhythmias but excludes planned diagnostic or interventional cardiac catheterisation, delayed chest closure, procedures for bleeding, institution of or weaning from ECLS, and non-cardiac surgical operations.
- **Acute neurological event:** New abnormality detected on clinical evaluation: coma; intracranial haemorrhage or stroke (confirmed on imaging); seizures (confirmed on electroencephalogram or obvious motor signs); or other neurological injury likely to result in a persistent or permanent deficit.
- **Sepsis:** defined broadly as severe infection leading to life-threatening organ dysfunction
- **Deep surgical site infection:** Surgical site infection and/or mediastinitis including any infection of an incised wound that undergoes any surgical reintervention within 30 days after the index operation or within the same hospital admission, independent of culture positivity.

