- **Other severe or life-threatening unexpected event:** Any other events which are severe or life-threatening must be formally assessed for relatedness (PI) and expectedness (CI).

If a patient fulfils more than one of the above SAE criteria, e.g. cardiac arrest requiring ECLS, a separate SAE form should be completed for each of the events.

The following events were classified as important morbidities but will not require expedited reporting: blood stream infection or endocarditis; feeding problems; necrotising enterocolitis; need for renal replacement therapy; and prolonged pleural effusion or chylothorax [3].

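### The protocol gives incompatible tests for when a related SAE is unexpected, so a related ECLS run, cardiac arrest or death outside the RSI could be classified either way

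*Protocol*

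**What the plan says.** Section 9.1 defines a SUSAR as "A SAR that is unexpected i.e. the nature, or severity of the event is not consistent with the applicable product information". Its entry for an unexpected adverse reaction, which a SUSAR must also satisfy, adds outcome: "When the outcome of an AR is not consistent with the applicable product information the AR should be considered unexpected". No list of events in the protocol plays a part in these definitions. Section 9.2 names the RSI: "For the purposes of the DESTINY trial, this will be the Investigator Brochure for del Nido cardioplegia", together with the SmPC for St Thomas' cardioplegia.

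Section 9.5 treats its list of complications as expected by protocol. Section 9.6 does the same for the graver events, including death, ECLS and cardiac arrest: "the following SAEs are protocol-defined as expected but must be reported in an expedited manner".

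Section 9.8 sets the CI's task: "The CI will also assess all related SAEs for expectedness with reference to the following criteria". The Expected row of Table 6 reads "An adverse event that is consistent with known information about the trial related procedures or that is clearly defined in the relevant safety information", and goes on to name the Investigator Brochure and the SmPC. The Unexpected row looks only at consistency with the trial procedures and does not mention the RSI. The sentence below the table then treats as unexpected an event that the protocol does not define as "an expected event or is not defined in the approved version of the RSI, it will be classified a Suspected Unexpected Serious Adverse Reaction".

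**The concern.** The CI must make one classification for each related SAE, and these sections do not lead to one answer. The events affected are the ones that would matter most if myocardial protection were inadequate. In section 9.6 the listed indications for ECLS include low cardiac output and poor cardiac function, and arrest, ECLS and death form part of the LCOS outcome.

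A related case is realistic. In Table 5 an assessment of 'possibly' counts as related, and under section 9.7.3 the CI cannot downgrade the site's causality judgement.

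Two reporting routes depend on the answer:
- **Regulatory (9.10.1):** a fatal or life-threatening SUSAR goes to the MHRA, main REC and Research Governance Team within 7 days, and other SUSARs within 15 days. An event classed as expected produces no SUSAR report.
- **DMC (9.10.2):** the Chair hears of a life-threatening SUSAR within 7 days. Other expedited SAEs wait for the next meeting, which section 14.5 schedules every 6-12 months unless an extra or emergency meeting is called.

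**Working it through.** No figure in the protocol is involved, so the check sets the tests side by side for a related SAE.

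Inputs:
- **Listed:** the event is on the lists in 9.5 or 9.6.
- **RSI covers:** the event is consistent with the Investigator Brochure or SmPC in nature, severity and outcome.
- **Assumption for the table:** a listed event is also consistent with the trial procedures, and an unlisted one is not. These are different criteria, and the assumption is relaxed below.

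| Related SAE | 9.1 | 9.5/9.6 lists | Table 6 | Sentence below Table 6, literal 'or' | Same sentence read as 'neither' |
|---|---|---|---|---|---|
| Listed, RSI covers | not SUSAR | expected | expected | not SUSAR | not SUSAR |
| Listed, RSI does not cover | SUSAR | expected | expected | SUSAR | not SUSAR |
| Not listed, RSI covers | not SUSAR | silent | meets both rows | SUSAR | not SUSAR |
| Not listed, RSI does not cover | SUSAR | silent | unexpected | SUSAR | SUSAR |

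1. The first and last rows agree under every test.
2. The second row is the case of a related ECLS run, arrest or death outside the RSI. With the literal 'or', section 9.8 disagrees with itself: the table says expected and the sentence says SUSAR. With 'neither', 9.8 agrees with itself and with 9.6, but all of them contradict 9.1. No reading brings every statement into line, and nothing in the protocol says which section prevails.
3. The third row is a separate fault that does not depend on 'or'. Because the Unexpected row omits the RSI, an event that is in the RSI but not consistent with the procedures meets both rows of Table 6.
4. Relaxing the assumption: suppose a listed event is unusual enough not to be consistent with the procedures, and the RSI does not cover it. Table 6 then gives unexpected, but 9.6 still gives expected and 9.1 still gives SUSAR. The conflict with 9.1 remains.

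**The case against.** **The sentence has a natural kinder reading.** It sits directly below a table that makes an event expected on either ground, and its bracket is never closed. 'Neither in the protocol nor in the RSI' is plausibly what was meant. This stands, so a reader who infers that 9.8 flatly contradicts itself on ECLS, arrest and death goes too far: that holds only with the literal 'or'. The conflict with 9.1 survives either reading.

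**Section 9.6 sets a reporting route and is not a test of expectedness.** This is fair as to its purpose, but it calls the listed events expected in terms, and the 9.8 sentence refers to what the protocol defines as expected. A reader might also infer that listed events escape the CI's assessment, because 9.6 asks for one by name only for other severe events. Section 9.8 rules that out, since it covers all related SAEs.

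**The RSI may cover these events.** If it does so at the observed nature, severity and outcome, every test agrees that the event is not a SUSAR. The protocol does not show the RSI's content, so the point is conditional.

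**Other safeguards exist.** Sites report every 9.6 event to BCTU within 24 hours (9.7.1). The CI reviews causality on each form (9.7.3), urgent safety measures are notified within 3 days (9.11), the TMG meets about monthly (14.3), and the DMC can meet in an emergency (14.5). These limit the harm, but none settles the classification or replaces a SUSAR report.

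**Conclusion.** The conflict is real but conditional. Section 9.1 judges unexpectedness by product information alone, while 9.5, 9.6 and Table 6 also accept protocol listing or consistency with the procedures. For a related ECLS run, arrest or death that the RSI does not cover, the CI could defend either classification. Table 6 also overlaps itself for events in the RSI that are not consistent with the procedures.

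The size per event is a 7- or 15-day report to the MHRA, REC and Research Governance Team, or none. For a non-fatal life-threatening event it is also notice to the DMC Chair within 7 days, or review at the next meeting. For deaths, the wording of 9.10.2 can be read as covering every death or only fatal SUSARs, so no effect on notice to the Chair is claimed there.

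A reader might infer that SUSARs will be missed in this trial. The protocol does not support that: it gives neither the RSI's content nor the share of events likely to be judged related, so no count of affected children is possible. The inconsistency should still be corrected.

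**What to change.** Apply the 9.1 test throughout.

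- **9.8, sentence below Table 6:** replace with *A related SAE is unexpected if its nature, severity or outcome is not consistent with the approved RSI; it will then be classified a SUSAR.*
- **9.8, Table 6:** make both rows refer to the RSI only.
- **9.5, 9.6 and the heading of 9.9:** change 'expected' to 'anticipated' where events are called expected by protocol. State that these lists set only the reporting route to BCTU and do not determine expectedness for SUSAR classification.
- **9.10.1 and 9.10.2:** no change is needed for this point.

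The cost is wording in 9.5, 9.6, 9.8 and one heading, with no new forms, data or meetings. The downside is possibly a few extra SUSAR reports for related listed events that the RSI does not cover, and none if it covers them. Dropping the literal 'or' also ends any need for SUSAR reports on unlisted events that the RSI already covers.

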## **9.9 Protocol defined expected SAEs**

Cardiac surgery with cardioplegic arrest in children may be associated with many anticipated serious adverse events in the early postoperative period, affecting one or more organ systems. We have defined above in section 9.6 which SAEs require expedited reporting to the sponsor.

## **9.10 Reporting SAEs to third parties**

### **9.10.1 Reporting to the Competent Authority and main Research Ethics Committee**

A minimal data set of all individual events categorised as a fatal or life threatening SUSAR to the Medicines and Healthcare products Regulatory Agency (MHRA), main REC and Research Governance Team (RGT) by BCTU within 7 days. Detailed follow-up information will be provided within an additional 8 days. All other events categorised as non-life threatening SUSARs will be reported within 15 days.

### **9.10.2 Reporting to the Data Monitoring Committee**

The Chair of the independent DMC will be notified of any death or life threatening SUSAR by BCTU within 7 days. All other SAEs requiring expedited reporting to the Sponsor will be reviewed at the subsequent DMC meeting. Details of all SUSARs and any other safety issue which arises during the trial will be reported to PIs. A copy of any such correspondence will be filed in the site file and TMF.

## **9.11 Urgent Safety Measures**

If any urgent safety measures are taken, BCTU shall immediately, and in any event no later than 3 days from the date the measures are taken, give written notice to the REC and MHRA of the measures taken and the circumstances giving rise to those measures.

## **9.12 Monitoring Pregnancies for Potential Serious Adverse Events**

Monitoring pregnancies is not applicable for this trial. All female patients of child-bearing age undergo pregnancy testing on admission prior to surgery; if positive, the patient would not usually proceed with surgery other than in an emergency, which is an exclusion for this trial.

## 10 DATA HANDLING AND RECORD KEEPING

### 10.1 Source Data

Source data is defined as all information in original records and certified copies of original records of clinical findings, observations, or other activities in a clinical trial necessary for the reconstruction and evaluation of the trial. To allow for the accurate reconstruction of the trial and clinical management of the subject, source data will be accessible and maintained from different sources (**Table 7**).

| Data                      | Source                                                                                                                                                                                                                                                                                                                                                                              |
|---------------------------|-------------------------------------------------------------------------------------------------------------------------------------------------------------------------------------------------------------------------------------------------------------------------------------------------------------------------------------------------------------------------------------|
| Lab results               | The original lab report (which may be electronic) is the source data and will be kept and maintained, in line with normal local practice. Information will be transcribed onto CRFs.                                                                                                                                                                                                |
| Imaging                   | The source is the original imaging usually as an electronic file. Data may be supplied to the Trials Office as a password-protected, anonymised, copy of the electronic file, or as an interpretation of the imaging provided on a CRF. Where data is interpreted, the CRF onto which it is transcribed becomes the source. Copy of the CRF should be provided to the Trials Office |
| Clinical event data       | The original clinical annotation is the source data. This may be found on clinical correspondence, or electronic or paper participant records.                                                                                                                                                                                                                                      |
| Trial-specific event data | The main trial CRFs are the source for data that would otherwise not routinely be recorded in the patient's medical record e.g. whether intraoperative biopsies were obtained, and time taken.                                                                                                                                                                                      |
| Recruitment               | The original record of the randomisation is the source. It is held on BCTU servers as part of the randomisation and data entry system.                                                                                                                                                                                                                                              |
| Drop out                  | Where a participant expresses a wish to withdraw, the conversation must be recorded in the medical record.                                                                                                                                                                                                                                                                          |

**Table 7.** Source data.

### 10.2 Case Report Form (CRF) Completion

A CRF is required and should be completed for each individual subject. The data held on the completed original CRFs are the sole property of the respective PIs whilst the data set as a whole is the property of the Sponsor and should not be made available in any form to third parties, except for authorised representatives or appropriate regulatory authorities, without written permission from the sponsor. Appropriate data sharing requests will be considered by the Sponsor.

It will be the responsibility of the investigator to ensure the accuracy of all data entered in the CRFs and confirm accordingly. The **DESTINY Site Signature and Delegation Log** will identify all those personnel with responsibilities for data collection.

The CRFs will comprise the following forms:

| Form Name                                  | Schedule for submission                                                                                  |
|--------------------------------------------|----------------------------------------------------------------------------------------------------------|
| Randomisation CRF                          | At the point of randomisation                                                                            |
| Baseline CRF                               | At the point of undergoing the index operation                                                           |
| Operation CRF                              | At the point of undergoing the index operation                                                           |
| Perfusion CRF                              | At the point of undergoing the index operation                                                           |
| Supplementary Perfusion CRF                | At the point of undergoing the index operation (if required)                                             |
| Postoperative CRF                          | At the point of hospital discharge                                                                       |
| Unplanned Reoperation/
Intervention CRF | At the point of undergoing each episode of further unplanned surgery or catheter intervention            |
| Serious Adverse Event CRF                  | Emailed within 24 hours of research staff at site becoming aware of an SAE requiring expedited reporting |
| Supplementary Serious
Adverse Event CRF | At the point of submitting a Serious Adverse Event CRF with additional medications (if required)         |
| Exit/Change of status CRF                  | At the point of change of status, withdrawal from the trial or death                                     |

**Data should** be submitted in a timely manner, therefore if data has not been provided within four weeks of the submission schedule detailed in **Table 8. Trial Case report forms**

Data reported on each form will be consistent with the source data and any discrepancies will be explained. Data should be submitted in a timely manner, therefore if data has not been provided within four weeks of the submission schedule detailed in *Table 8*, then a reminder email will be sent to sites. If the data has still not been received within 6 weeks, then the trial manager will directly contact the site via telephone to ascertain the reason for the delay. At 8 weeks from expected submission if the data still has not been received this may be escalated to site's senior management and can trigger a monitoring visit.

All missing and ambiguous data will be queried as per section 10.3.2. Staff delegated to complete CRFs will be trained to adhere to the **DESTINY CRF Completion Guideline**.

The following guidance applies to data and partial data:

- Date format: all dates should be recorded as dd-mmm-yyyy
- Time format and unknown times: all times should be in accordance with the 24hr clock
- Trial-specific interpretation of data fields: where guidance is needed additional information will be supplied
- Entry requirements for concomitant medications (generic or brand names): generic names should be used where possible
- Missing/incomplete data: should be clearly indicated, all blank fields will be queried by the trial office
- Repeat laboratory tests: the data used to inform clinical decisions should always be supplied. If a test is repeated, it is either to confirm or clarify a previous reading. Confirmatory tests should use the original test values. Protocol and GCP non-compliances should be reported to the Trials Office on discovery.

In all cases it remains the responsibility of the site PI to ensure that the CRF has been completed correctly and that data are accurate. This will be evidenced by the electronic signature, accessed by unique login, of the site PI on the CRF. Only CRFs specified in the protocol must be used.

